Eligibility criteria for this study reflects criteria of previous multi-component CS interventions. Participants must have a formal diagnosis of major neurocognitive disorder (dementia) as per the DSM-V criteria (American Psychiatric Association, 2013). Participants must have a mild-to-moderate cognitive impairment as classified by the Mini Mental State Examination (MMSE) or equivalent screens (Folstein et al., 1975). Individuals with severe dementia, i.e., an MMSE<10, will be excluded as most CS interventions are not applicable for those with severe cognitive impairment (Spector et al., 2003). Participants taking dementia medication can continue to do so during the study.

Participants must have some ability to communicate and understand communication, determined by a score of 1 or 0 on questions 12 and 13 of the Clifton Assessment Procedures for the Elderly-Behaviour Rating Scale (Pattie and Gilleard, 1979). Participants must be able to see and hear well enough to participate in the group. Participants will not be excluded if they have significant uncontrolled disruptive behaviours, a premorbid diagnosis of a learning disability, or a significant physical illness/disability that may affect participation during intervention sessions or assessments.

*Recruitment*

Participants will be recruited from HSE occupational therapy settings in Ireland. Clinicians will be encouraged to screen their case load for potential participants and approach them and their caregiver to discuss the study. If they are interested in taking part, internal referral protocols will be followed. Contact details will be passed to the research team who will arrange a meeting with the participant and their caregiver to assess eligibility. If they are eligible and agree to take part, informed written consent will be obtained. Participants’ capacity to consent to take part in the study will be assessed following the guidelines stipulated in the Assisted Decision-Making (Capacity) Act (2015). If the participant with dementia lacks the capacity to consent, appropriate protocols will be adhered to in line with the Assisted Decision-Making (Capacity) Act (2015) which is currently evolving into full enactment in Ireland.

*Randomisation and masking*

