**Intervention**

*CS-ADL*

The intervention group will receive a program of CS-ADL, with sessions delivered once weekly across 7 weeks. Typical CST programs commonly delivered by Irish occupational therapy services span a duration of 7 weeks, demonstrating that an intervention of this length is feasible within these services. CS-ADL sessions will last approximately 2 hours. While Ryan and Brady’s (2023) scoping review reported significant ADL benefits from the intensive multi-component CS interventions of Graessel et al. (2011) and Muñiz et al. (2015), Jiménez Palomares et al.’s (2021) occupational therapy CS program reported benefits for ADLs through a less intensive approach of two 45-minute sessions per week for a total of 5 weeks. As typical community-based CST programs often deliver two 45-minute sessions on the one day to aid feasibility, the planned intensity and duration of the CS-ADL program is therefore justified. At least one qualified occupational therapist will facilitate the sessions, with the assistance of a co-facilitator, as CS-ADL activities require a level of supervision not feasible for a single facilitator. Furthermore, the lead group facilitator must be an occupational therapist as the aims of CS-ADL align with the core principles of the profession. Each session consists of similar components, however the sequence and timing allocated per component may differ between sessions. Activities are based around a different theme for each session, for example morning routine, evening routine, or domestic activities, with each session intended to be enjoyable and mentally stimulating for the individual. A typical session will begin with 20-minutes of introductions, reality orientation, a group song and discussion of the news of the week. 15-minutes will then be spent on a physical activity/game. Physical activity will be a key component of the CS-ADL program as 7 of 9 CS programs reviewed by Ryan and Brady (2023) involving a physical activity component to intervention reported benefits for ADL outcomes. A physical activity at the start of the group will also aim to benefit arousal levels of participants and build rapport amongst group members. This will be followed by 25-minutes of ADL-focused cognitive stimulation activities, a 15-minute break, and approximately 10 more minutes of ADL-focused CS activities. These activities will include the identification and categorisation of everyday items, discussion, reminiscence, planning and sequencing of ADLs and the completion of everyday writing/calculation tasks. This will be followed by a 30-minute ADL task, which is an essential component to the program, as Ryan and Brady’s (2023) review found CS interventions with an ADL component report significant benefits for ADL outcomes. Examples of activities will include making a breakfast, a simple gardening activity or sorting laundry. While the structure of CS-ADL has taken inspiration from previous CS programs (Graessel et al., 2011; Jiménez Palomares et al., 2021; Spector et al., 2003), CS-ADL differs as participants are actively engaged in the planning, preparation, and practice of everyday activities like washing, dressing, and cooking. A full groupwork protocol and detailed session plans are available at Appendix 1 and Appendix 2.1 respectively. Sample handouts and instructional cards used in the implementation of CS-ADL sessions are available from appendix 2.2 to appendix 2.8. Therapists involved in the administration of CS-ADL are advised to use their clinical judgement in the planning and implementation of sessions, as sessions should be individualised to suit the needs, abilities, and interests of group members. Activities should be adapted accordingly.

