| **Group goals** | This group aims to:  -Provide opportunity for participants to receive peer support for memory and thinking challenges and/or the experiences of later life through a group environment.  -Provide a supportive environment in which participants with communication difficulties can express themselves amongst their peers.  -Provide benefits for cognition including improving the arousal levels of participants.  -Provide health benefits of exercise for participants through engagement in low-impact physical activity.  -Benefit mood of participants through opportunities to engage in physical activity, socialisation, and meaningful occupations.  -Provide an environment where participants are actively engaged and involved in the planning, preparation, and practice of ADLs.  -Increase participants confidence in the performance of ADLs.  -Introduce compensatory approaches to ADLs, providing opportunities for participants to explore compensatory devices and techniques of interest to them. |
| **Essential requirements for group membership** | -Older adults with a diagnosis of major neurocognitive disorder as per the DSM-V criteria (American Psychiatric Association, 2013).  -Group members must have a mild-to-moderate cognitive impairment, as assessed by the MoCA, or MoCA-Blind administered over the telephone. Individuals with severe cognitive impairment will not be suitable for group membership.  -Group members must have some ability to communicate and understand communication, determined by a score of 1 or 0 on questions 12 and 13 of the Clifton Assessment Procedures for the Elderly-Behaviour Rating Scale (Pattie and Gilleard, 1979).  -Individuals with significant uncontrolled disruptive behaviours, a premorbid diagnosis of learning disability, or a significant physical illness/disability that affects participation during intervention sessions will not be suitable for group membership. |

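### The trial's eligibility section and Appendix 1 contradict each other on three participant characteristics, which risks people being randomised and then refused the intervention in the CS-ADL arm only

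*Protocol*

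**What the plan says.** Protocol, Materials and methods, Eligibility criteria: "Participants will not be excluded if they have significant uncontrolled disruptive behaviours, a premorbid diagnosis of a learning disability, or a significant physical illness/disability". The sentence goes on to qualify the physical illness or disability as one "that may affect participation during intervention sessions or assessments".

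Protocol, Appendix 1, Essential requirements for group membership: this row starts from "Individuals with significant uncontrolled disruptive behaviours, a premorbid diagnosis of learning disability" and ends with people who have "a significant physical illness/disability that affects participation during intervention sessions will not be suitable for group membership".

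Appendix 1 is part of the trial plan, not background. The CS-ADL subsection of Intervention points to it: "A full groupwork protocol and detailed session plans are available at Appendix 1". Its Referral criteria row sends the reader to the eligibility criteria without saying which list is meant.

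On severity, the Eligibility criteria section asks for mild-to-moderate impairment "as classified by the Mini Mental State Examination (MMSE) or equivalent screens" and excludes an MMSE below 10 as severe. Appendix 1 asks for mild-to-moderate impairment "as assessed by the MoCA, or MoCA-Blind administered over the telephone" and rules out severe impairment without giving a score.

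**The concern.** A person in one of these groups passes the trial's eligibility rule and fails the rule for joining the intervention group. Staff at the two services cannot comply with both.

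The matter is statistical as well as editorial because the two rules act at different points. The trial rule is applied to everyone before allocation. The group rule concerns only people who are to attend CS-ADL, and usual care has no corresponding rule. If each rule is applied where it stands, any refusal falls after randomisation and in one arm. If nobody is refused, people whom the intervention's own protocol calls unsuitable attend sessions that include cooking and physical games, activities which the section on anticipated risks itself names as a source of risk.

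**Working it through.** The point rests on comparing texts. The arithmetic below only shows the scale under stated assumptions.

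**Step 1: the three characteristics side by side.**

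| Characteristic | Eligibility criteria | Appendix 1 | Conflict |
|---|---|---|---|
| Uncontrolled disruptive behaviour | not excluded | unsuitable | direct |
| Premorbid learning disability | not excluded | unsuitable | direct |
| Significant physical illness or disability | not excluded where it may affect sessions or assessments | unsuitable where it does affect sessions | only where participation in sessions is actually affected |

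**Step 2: the order of events.** Randomisation and masking puts eligibility, consent and baseline assessment before allocation. Intervention gives the group sessions to the intervention arm only. Treatment-as-usual contains no membership rule. So a person admitted under the first list meets the second list only if allocated to CS-ADL.

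**Step 3: what follows if that person is refused.** Two cases, depending on the analysis set:
- Followed up and analysed as randomised: non-receipt in one arm, which pulls the estimated effect towards zero.
- Dropped from the analysis: the CS-ADL arm loses a selected group that usual care keeps.

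**Step 4: scale.** The one documentary input is the total of 34 with 1:1 allocation (Trial design), so 34 / 2 = 17 expected per arm. The sample-size figure itself reproduces: a paired t-test with n = 34, d = 0.5 and two-sided alpha 0.05 gives critical t 2.0345 and power 0.8078, as stated. Nothing in this point changes it.

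The share q of affected people is not in the protocol. Assumed range 5% to 30%:
- Expected number in the CS-ADL arm, 17 × q: 0.05 → 0.9; 0.10 → 1.7; 0.20 → 3.4; 0.30 → 5.1.
- Analysed as randomised, assuming that those refused get no benefit, the effect E among attenders becomes (1 − q) × E: 0.95E at 5%, 0.70E at 30%.
- Dropped, assuming that their outcome is g SD worse, the unadjusted CS-ADL mean rises by q × g: 0.05 × 0.25 = 0.0125 SD at the low end; 0.20 × 1.0 = 0.20 SD; 0.30 × 1.0 = 0.30 SD at the high end.
- Statistical analysis plans a regression adjusting for baseline scores. If the deficit is already present at baseline and the slope of outcome on baseline is b, the shift falls to about q × g × (1 − b). With b assumed at 0.7 to 0.9, 0.20 SD becomes 0.20 × 0.3 = 0.06 to 0.20 × 0.1 = 0.02 SD.

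The two cases move the estimate in opposite directions, and all of q, g and b are assumed. No single figure can be defended.

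**Step 5: severity boundary.** The wording on equivalent screens lets the MoCA in, and both lists rule out severe impairment, so the instruments as such do not conflict. What is missing is a threshold. The secondary-outcomes section gives the MoCA 30 points and the MoCA-Blind 22, but no cut on either scale is set to correspond to the MMSE cut at 10.

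**The case against.** The strongest reply is that nothing in the protocol says anyone is removed after randomisation, or that a facilitator must turn anyone away. Under Recruitment the research team assesses eligibility at a meeting before consent, and under Appendix 1, Logistics, clinicians screen their caseload for the group. If the Appendix 1 list were applied at that stage it would fall on both arms alike. This stands, and it is why one-arm refusal is put here as a risk. It does not remove the contradiction: staff who screen by Appendix 1 would turn away people whom the eligibility section says are not to be excluded.

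The word not in the eligibility sentence may also be a slip. The sentence closes a series of restrictions and lists the same three groups in the same order as Appendix 1. That is plausible, but the document does not settle it, and sites work from what is written.

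Other parts of the reply also stand. The protocol provides a co-facilitator, clinical risk assessment and supervision, and tells therapists to adapt activities, so the safety side is not unattended. The diagnosis, the exclusion of severe impairment and the communication items agree in both lists, so the population is not wholly undefined. How refused participants are analysed is commonly left to a statistical analysis plan, which is not at hand, and its absence is not held against the protocol.

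**Conclusion.** The contradiction is real and lies in an operative eligibility rule. It is direct for disruptive behaviour and learning disability, and partial for physical illness or disability. Following both texts as written risks one-arm refusal after randomisation, with dilution if those refused are analysed as randomised and selection bias if they are dropped.

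A reader might infer that exclusions will certainly fall after randomisation in the CS-ADL arm, and that the result will be inflated by a sizeable part of the planned effect, for instance 0.20 SD against 0.5. The documents do not support this. No section describes such removals. The shift needs an assumed share, an assumed deficit, removal from the analysis and no baseline adjustment, whereas baseline adjustment is planned. The planned 0.5 is also defined for matched pairs, so it is standardised by the SD of differences and is not on the same scale as an outcome-SD shift. The size should be reported as unknown.

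A reader might also infer that the two lists demand incompatible screening instruments. They do not; only the matching threshold is missing, which is a secondary point.

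**What to change.** Reconcile the Eligibility criteria section and the Appendix 1 membership row into one list with the same wording, including one qualifier for physical illness or disability. The clinical team decides which version of the three criteria holds. State that the list is applied to every candidate before randomisation, so that it acts equally on both arms, and have the Referral criteria row of Appendix 1 point to that list by name. In the same edit, state the MoCA and MoCA-Blind thresholds that are to be read as equivalent to the MMSE cut, as chosen by the clinical team.

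The cost is a text correction before the first participant is screened. The protocol says that ethical approval is still being sought, so the correction can go in with that submission. If the stricter list is kept, the recruitment pool is somewhat smaller. No sample-size figure changes.

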**Materials and methods**

*Trial design*

This will be a multi-centre, parallel, single-blind, randomised superiority trial of CS-ADL versus TAU for people with mild-to-moderate dementia. Sample size was calculated using formal power analysis with G*Power software (Faul et al., 2007). Based on Cohen’s (1988) guidelines for small (*r =* 0.1), medium (*r* = 0.3) and large (*r =* 0.5) effects for a 2 (pre- and post-test) x 2 (CS-ADL and TAU) *t*-test, with the difference between two dependent means (matched pairs), sample size was calculated for an estimated small (*d =* 0.2), medium (*d* = 0.5) and large (*d* = 0.8) effect size. Two-tailed alpha of 0.05 was assumed for all tests. With an estimated effect size of 0.2, a sample size of 199 is required for a critical t of 1.9720175 and degrees of freedom (df) of 198, with an actual power of 0.8016910. With an estimated effect size of 0.5, a sample size of 34 is required for a critical t of 2.0345153 and a df of 33 and an actual power of 0.8077775. For an estimated effect size of 0.8, a sample size of 15 was calculated to be required for a critical t of 2.1447867 and a df of 14, with an actual power of 0.8213105. It is expected there will be challenges in the recruitment of 199 participant for the estimated effect size of 0.2, therefore for pragmatic reasons, recruitment will aim for the sample size of 34 (*d* = 0.5). Participants will be randomised with 1:1 allocation ratio to either the intervention or control group. The primary and secondary outcomes will be measured at baseline prior to randomisation and at the end of intervention (8 weeks). There will also be an observational assessment of occupational performance completed by the treating therapists within every group session.

*Study setting*

The study will take place in two Irish Health Service Executive (HSE), community-based occupational therapy services. The principal investigator will deliver the CS-ADL intervention.

*Eligibility criteria*

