Randomisation will occur after eligibility, consent and baseline assessments have been carried out. Random allocation will be completed by an allocator otherwise uninvolved in the study. A computer-generated number system (RANDBETWEEN Command on Microsoft Excel) will be used. While participants cannot be blinded to their allocated group, outcome assessors will be blind to group allocation.

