| **Frames of reference** | Activities will be based on a rehabilitative frame of reference (FoR). This FoR is typically used with individuals whose underlying difficulties are unlikely to be remediated and will therefore be used to inform this group as dementia is often of a progressive, degenerative nature (Gale et al., 2018). The rehabilitative FoR aims to maximise independence by utilising areas of strength rather than attempting to remediate areas of deficit. This will be achieved using cognitive stimulation strategies and ADL practice in conjunction with the instruction of compensatory methods like assistive equipment and memory aids. Members will also gain support from each other through group discussion and problem-solving of everyday scenarios. |
| **Logistics** | *Place of meeting:* Occupational therapy services. Group room to have adequate table and seating arrangements.  *Number of clients:* A closed group of approximately 5-10 individuals.  *Group facilitators:* The group will be facilitated by at least one qualified occupational therapist. Co-facilitation can be by fellow occupational therapist, healthcare assistant, student or relevant health and social care professional.  *Schedule:* The program will span 7 weeks, consisting of once weekly sessions lasting approximately 2 hours.  *Advertisement/promotion:* The group will be promoted to fellow clinicians within local services, who will screen their caseload for potential participants. |
| **Group structure** | Each session consists of similar components, however the sequence and timing allocated per component may occasionally differ between sessions. An example of the session structure is detailed below:  Sessions will begin with introductions, reality orientation, a group song, and a discussion of news of the week. This will be followed by warm-up exercises before a physical activity/game. ADL-focused cognitive stimulation activities will be completed before a 15-minute break, after which the main ADL-based activity will be completed. Sessions will be concluded with a group song. A full breakdown and method of each session is detailed below. |

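### Excel RANDBETWEEN, used as the protocol describes, does not guarantee balance by arm or service, or enough people for a closed group; a balanced list for each site cohort would be better

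*Protocol*

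**What the plan says.** - Ratio and size (Protocol, Trial design): "Participants will be randomised with 1:1 allocation ratio to either the intervention or control group", and "recruitment will aim for the sample size of 34".
- Setting (Study setting): "The study will take place in two Irish Health Service Executive (HSE), community-based occupational therapy services". How the 34 divide between the two services is not given.
- Mechanism (Randomisation and masking): "A computer-generated number system (RANDBETWEEN Command on Microsoft Excel) will be used". On who and when: "Random allocation will be completed by an allocator otherwise uninvolved in the study" and "Randomisation will occur after eligibility, consent and baseline assessments have been carried out". No restriction on the sequence and no stratification factor is mentioned.
- Delivery (Appendix 1, Logistics): "A closed group of approximately 5-10 individuals". The number of groups, the number of cohorts and the size of each intake are not given.
- Analysis (Statistical analysis): a regression adjusted for the baseline score, with sociodemographic covariates; age and gender are the examples.

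**The concern.** RANDBETWEEN returns a fresh random integer at each call. An allocator who follows the text literally, one draw per participant, carries out simple randomisation. In a large trial that would hardly matter. Here three features make it matter more.

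- The trial is small, so chance differences in arm size are large relative to the arms.
- There are two services. Usual care includes day-hospital activities for those who attend, so the comparator could differ by service. Chance imbalance of arm by service is not prevented by the method named.
- CS-ADL is a closed seven-week group, with baseline at week 0 and outcomes at week 8. If a draw leaves too few people for a group, the service must run it undersized, wait for more recruits or find another way to fill it. Waiting would stretch the time from baseline to outcome in one arm only.

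At stake are mainly workable groups and comparability by site. Precision is affected less.

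**Working it through.** **Inputs from the protocol.** N = 34, ratio 1:1, two services, group size about 5-10, effect size d = 0.5, and "Two-tailed alpha of 0.05 was assumed for all tests".

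**Assumptions, because the protocol is silent.** Each participant is allocated by an independent 50:50 draw. Cohort size m is unknown, so a range is shown.

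**1. The plan's own figure.** For a paired t-test with n = 34 and d = 0.5, df = 33 and the noncentrality is 0.5 × √34 = 2.915. The critical t is 2.0345 and the power 0.8078, as the protocol states. So 34 is the planned total. Whether a paired test is the right basis for it is a separate matter.

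**2. Overall balance.** The size of one arm is X ~ Binomial(34, 0.5), with SD √(34 × 0.25) = 2.92.

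| Split | Probability |
|---|---|
| Exactly 17:17 | 13.6% |
| 14:20 or worse | 39.2% |
| 13:21 or worse | 22.9% |
| 12:22 or worse | 12.1% |
| 11:23 or worse | 5.8% |

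**3. Balance within a service.** Assume 17 people at a service. P(more than 10 in CS-ADL) = 16.6%. By symmetry, P(more than 10 in TAU) is the same. A split of 11:6 or worse at that service therefore has probability 2 × 16.6% = 33.2%.

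**4. Enough people for a group.** The number in CS-ADL from a cohort of m is Binomial(m, 0.5), and P(fewer than 5) = Σ C(m, k) / 2^m for k = 0 to 4.

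| Cohort m | Calculation | P(fewer than 5 in CS-ADL) |
|---|---|---|
| 8 | 163 / 256 | 64% |
| 10 | 386 / 1,024 | 38% |
| 12 | 794 / 4,096 | 19% |
| 14 | 1,471 / 16,384 | 9% |
| 17 | 3,214 / 131,072 | 2.5% |

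**5. Cost in power.** This uses a two-sample t-test with d = 0.5, two-sided 0.05, N = 34 and no baseline adjustment. Relative efficiency is 4·n₁·n₂ / N².

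| Split | Relative efficiency | Power |
|---|---|---|
| 17:17 | 100% | 29.3% |
| 14:20 | 1,120 / 1,156 = 97% | 28.5% |
| 12:22 | 1,056 / 1,156 = 91% | 27.2% |
| 11:23 | 1,012 / 1,156 = 88% | 26.3% |

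The loss against 17:17 is 0.8, 2.1 and 3.0 points.

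**6. A balanced list for each site cohort.** A cohort of even size m puts m/2 in CS-ADL; an odd one puts (m − 1)/2 or (m + 1)/2. Every m from 10 to 20 then gives between 5 and 10, with certainty. Examples:

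- Sites of 17 and 17: 8 or 9 at each.
- Sites of 14 and 20: 7 and 10.
- Sites of 10 and 24, the larger run as two cohorts of 12: 5, 6 and 6.

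A cohort of 8 would give 4, so the list needs a planned cohort size beside it. Small blocks within site do not replace that planning: blocks of 4 at a site of 10 give 4 to 6, and at a site of 24 give 12.

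**The case against.** The best defence is that the text under-specifies the method and does not choose a poor one. RANDBETWEEN is only a number generator; an allocator could use it to put a balanced list in random order or to draw blocks. This stands: simple randomisation is the literal reading, inferred from silence about any restriction.

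Three stronger conclusions are tempting, and the documents do not support them.

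- A reader might infer that the method breaks the stated 1:1 ratio. It does not. The protocol promises a ratio, not 17:17, and fair independent draws have that ratio in expectation. What is missing is a guarantee of equal arms.
- A reader might infer that about a third of trials would have a service outside 5-10. That figure (1 − 0.809² = 35%) assumes 17 people per service and one group at each. Of the 19% outside the range at each service, 16.6 points are groups above 10, which could be divided in two, and the range is only approximate. The firmer problem is fewer than 5: 2.5% per service on the same assumption, and much more only if cohorts are smaller.
- A reader might infer that the sequence cannot be audited because the function recalculates. Nothing says the sheet would be left live, so this is not a finding.

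It is also fair that the power loss is slight, that chance imbalance is not systematic bias, and that model covariates may be left to an analysis plan that is not at hand. The absence of site from the listed covariates is therefore not counted as a fault.

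**Conclusion.** The point holds as a cheap improvement to the design, not as an error in the stated ratio. Used as written, the named method leaves three things to chance: equal arms, balance within each service and a workable group. The overall-balance figures rest only on independent 50:50 draws and N = 34. The within-service figure also assumes 17 people at a service. The group-size figures depend on a cohort size the protocol does not give and run from 64% (cohort of 8) to 2.5% (cohort of 17), so no single figure should be quoted for that risk. The direct loss of power is about 1-3 points and would not justify the change by itself; balance by site and groups that can run as planned do.

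**What to change.** In Randomisation and masking, keep the uninvolved allocator and replace unrestricted draws with the following.

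1. For each site cohort, a list with equal numbers of CS-ADL and TAU in random order (one extra place, assigned at random, if the cohort is odd), generated and fixed in advance.
2. Randomise the whole cohort together once its baseline assessments are complete.
3. Plan cohorts of about 10-20, so that each yields 5-10 in CS-ADL, and state the expected number of cohorts per service. A service with more than 20 recruits runs two cohorts.
4. Include site as a covariate in the baseline-adjusted regression, since it is then a stratification factor.

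Excel can still generate the list, and no extra staff or money is needed. There are two small downsides. Participants wait until a cohort is complete, so baseline assessments should fall close together. Allocation within a balanced list also becomes predictable towards its end if people are allocated one by one; allocating the whole cohort at once removes that.
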